## Abstract

**Introduction:** Intellectual Disability (ID) is the most common cause of referral to pediatric genetic centers, as it affects around 1–3% of the general population and is characterized by a wide genetic heterogeneity. The Genome Sequencing (GS) approach is expected to achieve a higher diagnostic yield than exome sequencing given its wider and more homogenous coverage, and, since theoretically, it can more accurately detect variations in regions traditionally not well captured and identify structural variants, or intergenic/deep intronic putatively pathological events. The decreasing cost of sequencing, the progress in data-management and bioinformatics, prompted us to assess GS efficiency as the first line procedure to identify the molecular diagnosis in patients without obvious ID etiology. This work is being carried out in the framework of the national French initiative for genomic medicine (Plan France Médecine Génomique 2025).

**Methods and Analysis:** This multidisciplinary, prospective diagnostic study will compare the diagnostic yield of GS trio analysis (index case, father, mother) with the French core minimal reference strategy (Fragile-X testing, chromosomal microarray analysis and Gene Panel Strategy of 44 selected ID genes). Both strategies are applied in a blinded fashion, in parallel, in the same population of 1275 ID index cases with no obvious diagnosis (50% not previously investigated). Among them, a subgroup of 196 patients are randomized to undergo GS proband analysis in addition to GS trio analysis plus the French core minimal reference strategy, in order to compare their efficiency. The study also aims to identify the most appropriate strategy according to the clinical presentation of the patients, to evaluate the impact of deployment of GS on the families’ diagnostic odyssey and the modification of their care, and to identify the advantages/difficulties for the patients and their families.

**Ethics Statement:** The protocol was approved by the Ethics Committee Sud Méditerranée I and the French data privacy commission (CNIL, authorization 919361).

**Trial Registration:**
ClinicalTrials.gov identifier NCT04154891 (07/11/2019).

## Introduction

The advent of Next Generation Sequencing (NGS) technologies has revolutionized our approach to diagnosis and research in the field of rare diseases at an international level, prompting rapid efforts to deploy these technologies in many countries, and by the European Commission (“1 + Million Genomes Initiative”, launched in 2018). In the same spirit, the 2016 launch of the French plan for genomic medicine (AVIESAN, 2016) was designed to serve a range of medical disciplines, including cancer and rare diseases. The France Genomic Medicine 2025 plan cited rare diseases as one of the key areas at the forefront of NGS implementation, to improve patient care, shorten their diagnostic odyssey and boost research. Indeed, genetic diagnosis is the first step towards appropriate care, follow-up and genetic counseling. Moreover, enhancing our understanding of pathogenesis could help to elaborate more specific therapies. The general goal of French Genomic Medicine plan is to implement the use of Genome Sequencing (GS) in France within the next 10 years, by creating national sequencing platforms (2 of which are now fully operational), and as a kick off, to implement four pilot studies, one of which is dedicated to rare diseases, namely the DEFIDIAG pilot study.

This DEFIDIAG pilot study focuses on intellectual disability (ID), as one of the most challenging models of rare disease. ID affects around 1–3% of the general population, with around 15 per 1,000 persons having mild ID and around 3 per 1,000 having severe ID. It is the most common cause of referral to pediatric genetic centers. ID results from abnormal brain development due to numerous possible cellular processes, including neuron proliferation and differentiation, neuron or astrocyte metabolism and maintenance, neurotransmitter synthesis, receptor or signal transduction, transcriptional and translational control. It is also well recognized that ID may result from non-genetic causes (neonatal anoxia, toxic effects, deprivation … ) or from genetic causes. Gene and chromosomal variations involved in human ID are numerous and include recurrent chromosomal events from complete chromosomal duplication, segmental chromosomal duplication or deletion, or small genic variations altering the function one among more than 1,500 genes such as single nucleotide variants (SNV), insertions or deletions (indel), unbalanced (CNV) or balanced structural variants (SV) in coding or non-coding regions, or even rarer events such as repeat expansions, uniparental disomy, mobile element insertion etc., which are reported in the OMIM registry. Approximately 15% of ID is attributable to cytogenetically clear-cut abnormalities, with at least two-thirds of these cases accounted for by trisomy 21 (Ellison et al., 2013) and up to 40% to one variation in one of the 1500 ID gene when exome sequencing is performed (Han and Lee, 2020).

Before next generation sequencing methods, genetic testing was limited to traditional karyotype and fragile X analysis, sometimes with gene specific Sanger analysis, when a specific syndromic ID was suspected. In the past 10 years, microarray analysis (CMA) has been widely used for the genetic diagnosis of ID. NGS tests recently emerged, in the last 5 years, with gene panel approaches and Whole Exome Sequencing (ES) following CMA and fragile X syndrome screening. Today, the question arises about the input of whole genome sequencing as a first approach in such patients, as this may profoundly modify the testing process by replacing CMA and other sequencing approaches (specific genes, panel, ES) and in addition, may detect new molecular mechanisms not detectable by CMA and ES.

Nowadays, most patients with no clinical diagnosis in France still undergo basic investigation (Fragile X and CMA) with a diagnostic yield of less than 20%. This basic exploration is usually followed by additional analysis using gene panel approaches containing at the very least a minimal core of 44 genes, namely the 44GPS minimal list recommended by the French national association of molecular genetics practitioners (Association Nationale des Praticiens de Génétique Moléculaire, ANPGM). The panel sequencing in the proband gives an additional diagnostic yield of 10–12% (using the 44 gene panel), and up to 40% (Han and Lee, 2020) in case of ES. ES as the first line test for the diagnosis of rare genetic diseases has recently been shown in some countries to be cost-effective, tripling the diagnostic rate at one third of the cost, in children with suspected monogenic disorders (Stark et al., 2017; Schofield et al., 2019). There is also emerging evidence of the efficiency of GS over standard testing (Alam and Schofield, 2018). However, the heterogeneity in clinical presentation, sample sizes and health economic evaluation standards makes it difficult to generalize the first published results (Schwarze et al., 2018) to other settings. A recent study in Ontario, Canada reported that GS might have a higher diagnostic yield than standard genetic testing, and could be a cost-effective strategy when used after standard testing or when used earlier in the diagnostic pathway (Ontario Health (Quality), 2020). However, these results need to be confirmed in the French setting since marked differences exist between countries in the technologies used, the costs, and the organization of clinical, biological and bioinformatics pathways.

Against this background, the DEFIDIAG study aims to evaluate the diagnostic performance and cost-effectiveness of GS as a systematic and unique molecular investigation for French patients with ID of unknown etiology, compared to the standard minimal protocol defined by the ANPGM, under conditions close to routine. Indeed, GS provides an opportunity to analyze a wider panel of molecular events, such as: 1) SNV and insertion/deletion (indel) in coding regions, even in CG rich regions, 5′ and 3′ UTR, promoter or intronic regions; 2) unbalanced chromosomal anomalies (CNV), with greater accuracy due to homogeneous coverage; 3) balanced structural variants, such as inversion and translocation, and lastly, 4) mechanisms observed very infrequently, such as uniparental disomy for imprinted chromosomal regions or insertion of mobile elements. Genome analysis was chosen because potential splice site mutations in deeper intronic regions are not enriched by exome analysis; CNV in exome enrichment strategies are still not 100% sensitive, specific and reliable; partial inversions or translocations affecting coding regions are not found by ES, and promoter or regulatory regions are not analyzed by ES.

This study also includes impact studies, aiming to assess the perceived impact for patients and their parents, for whom this technique may herald the end of their diagnostic odyssey. To this end, the DEFIDIAG study involves 15 medical genetics departments with strong clinical expertise in ID patients, as well as six diagnostic laboratories with a proven track record of competence in ID gene exploration, and the national sequencing platform of the National Center of Human Genomics Research (CNRGH), recognized for the high quality of its genomic sequence production and bioinformatics processes.

Specifically, the primary objective of this study is to compare the percentage of causal genetic diagnosis identified by GS performed on a trio (the patient and both parents) (GST), to the use of the current French reference minimal strategy (Fragile X + CMA + 44GPS) in ID patients attending a first genetics consultation. Secondary objectives focus on the diagnostic yield, and include the following:• To compare the percentage of ID causal diagnosis identified by GST, to GS in the proband only (i.e., genome in solo, GSS) in a subgroup of randomized patients attending for a first genetic investigation. This evaluation is useful because in genetic counseling, both parents are not always available.• To describe the estimated additional diagnostic yield that would be obtained at each step in sequential analysis of the GS data: for the minimal 44GPS gene panel, the list of genes known to be associated with disease from OMIM (referred to simply as OMIM), and ES, in patients attending for a first investigation (never-explored patients) and in patients who have already undergone investigations (previously-explored patients).• To compare the percentage of causal diagnosis of ID identified by GST to that obtained with the French reference minimal strategy in various subgroups (defined according to age, severity of ID, presence of major non-cerebral manifestations or epilepsy), for patients with ID attending for a first genetic investigation (never-explored patients).• To compare the percentage of causal structural changes (CNV, balanced structural variants) identified by GST versus CMA.• The DEFIDAG study also aims to compare the reference strategy, GST and GSs, in terms of costs and effectiveness for the causal diagnosis of ID in patients with ID of unknown etiology, attending for a first genetic investigation.• Finally, three impact studies are planned. The first will estimate the costs associated with searching for a molecular diagnosis that could potentially be avoided by performing GS as the first line approach. The second will evaluate the impact on the frequency and type of medical, medico-social and psychological care in the year following the release of GS results, compared to care during the year prior to inclusion, in particular in patients who were already engaged in a diagnostic process prior to being invited to participate in the DEFIDIAG study. The third impact study will be performed in two centers, and will use a qualitative approach, namely interviews with a sample of parents, to explore: 1) the burden experienced by the parents, 2) emotional adjustment of the patient and the parents to the results of genetic tests, and 3) the patient and parents’ perception of the future.

## Methods and Analyses

### Study Setting

The DEFIDIAG study is a prospective multicenter diagnostic study comparing two main strategies (namely GST versus the minimal reference strategy) applied in a blinded fashion to consecutive patients with no obvious clinical diagnosis, referred to medical genetic departments. Each patient included serves as their own control, and will undergo both strategies being compared. In parallel, the percentage of ID causal diagnosis identified by GSS, as compared to GST, will be evaluated in a randomized subgroup of patients attending a first genetic investigation.

In addition to the prospective diagnostic study, we will also perform quantitative impact studies to collect data concerning management of patients before inclusion, during the genetic analyses process, and after the results are made known (Figure 1); as well as a qualitative substudy using interviews (one interview after inclusion, a second interview after the results are made known to the parents/patients, and a third and final interview 12 months after the results are made known) in a sample of parents. The target population for each objective is described in Table 1.

**FIGURE 1 F1:**
[figure not shown]
Impact study procedures and schedule (DEFIDIAG study). The figure represents the key timepoints for patient visits in the inclusion centers (inclusion in the study, delivery of results, 12-months post-delivery visit), which also correspond to the time of the interviews between either a sociology or psychology researcher and the parents/patients who agreed to participate in the qualitative impact study. The figure also shows the three periods considered for cost estimation (period 1: before inclusion; period 2: waiting for results; period 3: during the 12 months following the results) and, for each of these periods, the different elements collected from the care teams and families in order to have the examinations carried out (for the three periods) and those envisaged with each of the strategies to confirm the diagnosis (period 2).

**TABLE 1 T1:** Correspondence between objectives and target population (DEFIDIAG study).

Eligible index cases (*n* = 1,275)	
**Index cases with undiagnosed ID coming for the first time for a genetic investigation (*n* = 637)**	**Index cases with undiagnosed ID already investigated (*n* = 637)**
Primary objective: Compare the percentage of genetic causal diagnosis identified in ID patients by performing trio GS analysis vs. the use of the current French reference minimal strategy	
Secondary objective: diagnostic yields	
•Compare the percentage of ID causal diagnosis identified by GST vs. the reference strategy in different subgroups (defined according to age, or clinical manifestations)	
•Compare the percentage of causal structural changes identified by GST vs. chromosomal microarray analysis	
•Compare the percentage of ID causal diagnosis identified by GST vs. GSS in a subgroup of randomized patients (*n* = 196)	
Secondary objective: Describe the estimated additional diagnostic yield that would be obtained at different steps of sequential analysis, for the 44 gene panels, OMIM and exome analysis	
Secondary objective: Assessing the efficiency of the three strategies (the reference minimal strategy; GSs; GS_T_)	
	Secondary objective: Estimate the cost of the diagnostic odyssey that could be potentially avoided by first-line genomic analysis
Secondary objective: Estimate the frequency and nature of changes in medical follow-up of the patients, but also in medico-social, rehabilitation, and psychological follow-up in the first year after the reporting of GS analyses compared to the period before the inclusion	
Secondary objective: Evaluate the burden experienced by the parents, 2) the parents’ emotional adjustment to the primary genetic tests results, and 3) the parents’ perception of the future	

GS_T_: genome sequencing—trio analysis; GS_S_: genome sequencing—proband only.

### Strategies Compared

In order to avoid producing redundant sequences, for each patient included, one unique set of genomic data sequences will be produced by a unique sequencing platform (CNRGH, Evry, France). Analyses are then performed blindly by two independent mirror laboratories: one laboratory will analyze the genome with the parental inheritance information (GST), while the second will analyze only the 44 genes of the reference minimal strategy (44GPS), without parental inheritance information, as well as the proband genome (GSS) in a randomized selection of patients (Figure 2; Supplementary Table S1).

**FIGURE 2 F2:**
[figure not shown]
Sample flow description (DEFIDIAG study). C: Clinical centers; L: Reference laboratory (highlighted in light yellow) and Mirror Laboratory (highlighted in dark yellow); MDM: MultiDisciplinary meeting; CNRGH: Centre National de Recherche en Génomique Humaine (National Centre for Human Genomic Research). Each clinical center (C, numbered 1–12) is affiliated to one reference laboratory (numbered 1–6) in charge of the analysis of trio-genome sequencing—GST; each laboratory (L) is affiliated to 2 clinical recruitment centers as a reference laboratory (for example: L1 will be the reference laboratory for patients from C1 and C2) and will work in pairs with another laboratory (mirror laboratories), in charge of ID44 and of the analysis of solo-genome sequencing (GSS) for patients randomized in the appropriate sub-group. This mirror laboratory is itself affiliated with two other recruitment centers (for example: L1 will be the mirror laboratory for patients from C3 and C4). The 4 clinical centers organize the multidisciplinary meeting (MDM) together with their 2 official laboratories.

The results of the 44GPS will be withdrawn from the GS data for all patients, using a specific bioinformatics filtering procedure that mimics the results obtained using targeted capture analysis (exons ± 20 intronic bases, SNV and CNV analysis). Fragile-X and CMA (included in the reference strategy) follow the routine care circuit, which is mainly independent of the GS circuit.

GST analysis is performed following a harmonized, consensus protocol adopted by the six clinical laboratories involved in this study, and using a common web interface (Polyweb.fr, developed in-house at the Genetic diseases IMAGINE Institute, Paris, France). All genomic variations are called by standard callers (GATK and BWA) and are subsequently ranked using several factors to facilitate analysis (protein impact, inheritance model, ID known gene and control data bases, splice prediction effect … ) in the Polyweb interface. For the SNV/small indel, the scheme contains a first minimal filtration step (for SNV/indel, elimination of the variations with over 1,000 hits in GnomAD, or 5 hits at homozygous state). All variations with a predicted protein impact are ranked at the top of the list and will be studied even when a first deleterious causative variation is detected. This broad approach ensures that co-occurring mutations in different genes will be identified [multi allelism is expected in about 5% of the cases (Yang et al., 2014)]. Additional bioinformatics modules such as repeat tracking, promoter and evolutionary conserved regions analysis, and mobile element insertion detection will be implemented and applied onto negative genome results during the ongoing protocol. Specific protocols for the proband GS data and 44GPS analysis are also developed and shared between the six laboratories. To limit time dedicated to GS proband analysis, SNV/indel analysis only focuses on exonic ± 20 bases of the known ID genes (SysID list) and OMIM disease-associated genes.

When the analysis is completed, variants of interest (highly suspected to be pathogenic) are recorded in a dedicated and secured electronic Case Report Form (e-CRF). Variant class (pathogenic as class 5 variant, probably pathogenic as class 4 variant or of unknown significance but highly suspected to be pathogenic as class 3 + variant) is validated during a Multi-Disciplinary Meeting (MDM) before being communicated to the patient.

The results of the microarray analysis and Fragile X analysis will be communicated to families and collected in the dedicated e-CRF by the recruiting genetic team as soon as the results are obtained from the diagnostic laboratories. The laboratories in charge of the GS analyses will remain blinded to these results. The GS results will be available approximately 6–9 months after inclusion in the study. In the event of an emergency (such as pregnancy), the blinding can be lifted and the results delivered to families as soon as they become available.

### Study Endpoint

#### Primary Outcome

The primary study endpoint is the identification of a causal diagnosis of ID, defined as the identification of one or more class 4 or 5 variant(s) that explain the symptoms presented by the patient, and validated during a specific MDM.

#### Secondary Outcomes

• Efficacy in terms of diagnostic yield: identification of causal structural changes• Efficiency: estimation of the incremental cost-effectiveness ratio, expressed in terms of cost per additional positive diagnosis.• Quantitative impact studies• Cost of the diagnostic odyssey: mean cost related to the iterative search for a diagnosis in the previously investigated population.• Change in follow-up: criteria will be the change in the number and type of medical, medico-social, rehabilitative, and psychological care induced by the results of the trio genomic analyses.• Qualitative impact studies: A sociologist and a clinical psychologist will explore the consequences on the family, and on the personal, professional and social life of the parents who take care of a child or an adult with ID, as well as the emotional adjustment and possible information overload for the parents at the various stages of the study (inclusion, results rendering, 12 months after receiving results).

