The strategy based on GST is expected to yield a diagnosis in at least 60% of patients with ID versus 30% with the reference minimal strategy in the population of patients attending for a first genetic investigation (never-explored patients). However, the strategies will be compared in 7 subgroups: 1) 3 defined by age: children <2 years old/2–5 years/>5 years; 2) 4 subgroups of patients defined according the severity of ID, and/or 3) with associated manifestations:1) mild ID associated with another sign, 2) moderate to severe ID, 3) ID with major non-cerebral abnormality, and 4) ID associated with epilepsy The smallest sub-group (subjects with mild ID associated with another significant sign) should represent around 15% of the total population, and the difference between the GST and the reference strategy in this particular subgroup can be assumed to be less than 15%. In addition, it is assumed that fewer than 1% of diagnoses identified with the referral minimal strategy will not be identified by the GST. Finally, we will also compare GST and GSS in a subgroup of randomized patients referred for the first time. For this specific comparison, a difference of 7% is expected, and <0.1% of diagnoses identified by GSS and not by GST. Considering these 9 planned comparisons (8 comparisons between GST and the reference strategy and 1 between GST and GS), the one-sided alpha risk is fixed at 0.00278. Based on these hypotheses, and a power of 80%, among patients seen for a first genetic investigation (50% of the population to be recruited), 41 patients are required for the main comparison, and 91 patients with mild ID + other syndrome are necessary. To recruit this number of patients, we estimate that it will be necessary to screen 607 patients attending for a first referral. A subgroup of 196 patients will be randomized to undergo GSS in addition to GST plus the reference minimal strategy. The sample size for this subgroup will be sufficient to compare GST and GSS in terms of diagnostic yield, as well as in terms of efficiency (a sample size over 150 is usually deemed sufficient). As we intend to include 50% of patients attending for a first genetics evaluation (never-explored patients), and 50% of patients who have already been investigated (previously-explored patients), a total of 1,214 patients are necessary. Considering that approximately 5% of samples will not be analyzable, it will therefore be necessary to include 1,275 index cases plus both their parents, for a total of 3,825 participants.

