#### Impact Studies

The costs of finding a diagnosis will be described only in the population of patients who had previously had genetic investigations (50% of the 1,275 index cases), as the mean and standard deviation, if normally distributed, or as median and interquartile range otherwise.

The analysis of the impact of genomic analysis on medical, medico-social, rehabilitation and psychological follow-up after the results are made known, will be performed separately in the previously-explored population (50% of the 1,275 index cases) on the one hand, and in the population attending for a first genetics investigation on the other hand (never-explored patients). Frequencies of follow-up changes between the period prior to inclusion and the period following the results will be calculated with associated 95% confidence intervals. A global analysis will then be performed, regardless of the results of GST. Sub-analyses will be conducted according to the result of GST: positive, negative or uncertain.

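### In never-explored patients, the change-in-care endpoint credits the trio genome result with changes that CMA or Fragile X results, released during the wait, may have caused; up to about a third of trio-positive patients could be affected

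*Protocol article*

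**What the plan says.** The Secondary Outcomes section sets the change-in-follow-up criterion as "change in the number and type of medical, medico-social, rehabilitative, and psychological care induced by the results of the trio genomic analyses". The Impact Studies section of the methods makes it a before-after comparison of period 3 with period 1. The Figure 1 legend defines period 1 as before inclusion, period 2 as the wait for results, and period 3 as the 12 months after results.

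The Impact Studies part of the data analysis section analyses previously-explored and never-explored patients separately. It plans frequencies of change with 95% confidence intervals and a global analysis, and then: "Sub-analyses will be conducted according to the result of GST: positive, negative or uncertain". It names no other split.

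Under Strategies Compared, CMA and Fragile X follow the routine care circuit, and their results "will be communicated to families and collected in the dedicated e-CRF by the recruiting genetic team as soon as the results are obtained". Genome results are expected about 6–9 months after inclusion. The 44-gene panel (44GPS) result is filtered out of the genome data, so it is not available early.

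**The concern.** The before-after contrast spans the waiting period, and in never-explored patients another diagnostic result can be released within it. Take a child with a pathogenic copy number variant. The family can learn of it from CMA during period 2, and follow-up can change then. GST finds the same variant, and the child enters the GST-positive group. Any change that lasts into period 3 is then counted as induced by GST. A split by GST result alone cannot separate this child from one whose diagnosis was first returned at the genome visit.

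The closing part of Ethics and Dissemination says the study should show the effect of genome sequencing on patient care and support a decision on first-line use. Never-explored patients are the first-line population. If the figure is read as what GST adds to the routine tests, it includes the effect of the comparator's own tests.

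**Working it through.** **Inputs, all from the protocol article**
- Yields in never-explored patients (Population): "at least 60% of patients with ID versus 30% with the reference minimal strategy".
- CMA plus Fragile X (Introduction): less than 20%, a ceiling.
- 44GPS, in addition to those tests (Introduction): 10–12%.
- Overlap (Population): the plan assumes that "fewer than 1% of diagnoses identified with the referral minimal strategy will not be identified by the GST".
- Patients: 607 analysable never-explored patients (Population). Table 1 gives 637, which includes the roughly 5% of samples expected not to be analysable.

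**Step 1: reproduce the plan's reference yield.** 20 + 10 = 30% and 20 + 12 = 32%, against 30% stated. The components agree with the total when the basic yield is near its ceiling.

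**Step 2: the part returned early.** Only CMA and Fragile X count. Reference yield minus panel yield: 30 − 12 = 18 points and 30 − 10 = 20 points.

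**Step 3: share of GST-positives.** If GST re-finds nearly all of these, the share is the early yield divided by the GST yield: 18/60 = 30.0% and 20/60 = 33.3%. If a full percentage point of all patients were missed by GST and all of it came from CMA or Fragile X, the range is (18 − 1)/60 = 28.3% to (20 − 1)/60 = 31.7%.

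**Step 4: counts.** GST-positive: 0.60 × 607 = 364. Already diagnosed: 0.18 × 607 = 109 to 0.20 × 607 = 121.

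**Step 5: sensitivity to the ceiling.** With the GST yield held at 60%, an assumed basic yield of 15% gives 15/60 = 25%, and 10% gives 10/60 = 17%. A GST yield above 60% lowers every share.

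**Step 6: composition of 60 GST-positives on the planning figures, ignoring the small loss to GST**

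| Group | Per 60 | Of 364 |
|---|---|---|
| (a) already returned from CMA or Fragile X | 18–20 | 109–121 |
| (b) first returned at the genome visit, also made by 44GPS | 10–12 | 61–73 |
| (c) made by GST only | 60 − 30 = 30 | 182 |

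**The case against.** The strongest reply is that the study assesses genome sequencing as a single first-line investigation that could replace CMA. On that view, a variant found by GST is a GST diagnosis whichever test reported it first, and the care that follows is part of its impact. CMA runs in parallel only because each patient is their own control. This stands against removing group (a) from the main estimate: doing so would give a selected picture of first-line sequencing. It does not justify attributing to GST, without qualification, a change that followed an earlier result.

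A second reply is that the analysis is descriptive, with no test and no contrast between strategies, and that a further split may sit in an analysis plan not shown. The first part is true, and it limits the severity. But the article itself states both the causal wording and the split by GST result, so the point is not just missing detail.

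Third, the objectives in the Introduction place particular emphasis on patients already engaged in a diagnostic process. They enter undiagnosed after earlier work-up and are analysed separately, so the problem largely passes them by. This stands, and the point is confined to never-explored patients.

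Fourth, the CMA and Fragile X turnaround is not stated. A reader might infer that families learn of the diagnosis months earlier. The article supports only immediate release against about 6–9 months for the genome result; the length of the lead, and how much care changes within it, are unknown.

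**Conclusion.** The point holds for never-explored patients. As stated, the analysis cannot attribute the period 1 to period 3 change to GST, because CMA and Fragile X results are released in between and the only planned split is by GST result. Up to about a third of GST-positive never-explored patients could already hold the diagnosis: 30–33%, about 109–121 of 364.

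This rests on planning yields, a basic yield near its ceiling, a GST yield at its floor, near-complete overlap, and CMA or Fragile X results reaching the family before the genome visit. It is not an observed proportion.

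Two stronger readings are tempting. One is that the benefit of genome sequencing is overstated outright. The documents support this only for benefit beyond the routine tests, and only for changes that persist into period 3; changes that start and end in period 2 are missed instead. The other is that the whole impact study is compromised. It is not: previously-explored patients are largely unaffected, and the overall before-after figure remains a valid description of change after the complete work-up.

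**What to change.** In the Impact Studies part of the data analysis section, keep the overall GST-positive estimate but describe it as change after the whole work-up, and align the wording of the secondary outcome. Then report GST-positive never-explored patients in three groups:

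- (a) same diagnosis already returned from CMA or Fragile X before the genome visit;
- (b) diagnosis first returned at the genome visit but also made by 44GPS;
- (c) diagnosis made by GST only.

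Limit any claim of care change attributable to GST beyond the routine tests to (b) + (c), and any claim of gain over the reference strategy to (c).

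The results are already collected: CMA and Fragile X results are "collected in the dedicated e-CRF by the recruiting genetic team as soon as the results are obtained from the diagnostic laboratories", and the multidisciplinary meeting records its conclusions for the different approaches. Group (a) also needs the date on which the family was told. The article does not say that this date is recorded; if it is not, the e-CRF entry date could stand in.

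The cost is precision. For a proportion of 50%, the widest case, the 95% half-width is 1.96 × √(0.25/n). That is 5.1 points for all 364 GST-positives, 6.1–6.3 points for (b) + (c) with 243–255 patients (364 − 121 to 364 − 109), and 7.3 points for (c) with 182.
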